## Abstract

**Background:**

Dysphagia is a major complication following ischemic stroke, but lacks effective treatments. Our previous studies show specific mode electroacupuncture stimulation (SMES) is an alternative approach to open the blood–brain barrier (BBB). Delivery of NGF across the BBB by SMES may be effective for treating dysphagia after ischemic stroke. The aim of this study is to assess the efficacy and safety of SMES combined with NGF for dysphagia after ischemic stroke.

**Methods:**

A total of 144 participants will be randomly assigned to an electroacupuncture (EA) + NGF group, an EA + placebo group, an acupuncture + NGF group, or an acupuncture + placebo group in a ratio of 1:1:1:1. Patients will receive 18 sessions of treatment for 6 weeks and a follow up of 6 weeks. The primary outcome is the Functional Oral Intake Scale (FOIS), and the secondary outcomes are the Dysphagia Outcome and Severity Scale (DOSS), the Penetration Aspiration Scale (PAS), the modified Rankin Scale (mRS), and the Modified Barthel Index (MBI). The functional near-infrared spectroscopy (fNIRS) will be applied to detect the changes in neurological function. Additionally, blinding and safety will also be assessed. All analysis will be performed based on intention-to-treat.

**Discussion:**

This trial will explore the feasibility and provide potential evidence for the effectiveness and safety of SMES combined with NGF for dysphagia after ischemic stroke.

**Clinical trial registration:**

https://www.clinicaltrials.gov/ct2/show/NCT06737549, identifier (NCT06737549).

## Introduction

Dysphagia is a major complication following acute stroke (1), with an incidence of 78% (2). Post-stroke dysphagia (PSD) can have a long-term impact on the dietary and nutritional intake of survivors, and even lead to pneumonia, or increase the hospitalization rate and mortality. Currently, non-pharmacological treatments, including dietary and nutritional interventions, behavioral treatment, dedicated oral health care, and peripheral or central neurostimulation strategies (3, 4), have demonstrated greater efficacy than pharmacological treatments for PSD. However, more evidence is needed to prove the effectiveness of non-pharmacological treatments for PSD (5). Pharmacological treatments for PSD, such as transient receptor potential cation channel subfamily V member 1 (TRPV-1) receptor agonists, angiotensin converting enzyme (ACE) inhibitors or dopaminergic agents, are generally administered only in research settings, due to the limited evidence available with regards to clinical endpoints (3, 4).

Nerve growth factor (NGF) is a neurotrophic substance that exhibits remarkable neurorepair and neuroprotective properties, displaying an active role in nourishing nerves, promoting neuronal survival, and inhibiting apoptosis (6). The advent of NGF offered a promising option for the treatment of central nervous system diseases. However, its actual clinical efficacy is less than satisfactory. The main issue lies in the fact that NGF, with a molecular weight of 13.4 kDa, is too large to cross the blood–brain barrier (BBB), preventing it from achieving effective blood concentrations in the central nervous system and limiting its application in central nervous system diseases (7). Therefore, one of the current focuses of neurological rehabilitation research is how to transport NGF and other large molecule neurotrophic drugs across the BBB to brain tissue, to achieve effective blood concentrations and exert their neurotrophic effects.

Previous research by our team has demonstrated that applying specific mode electroacupuncture stimulation (SMES) to the GV20 (Baihui) and GV26 (Shuigou) acupuncture points could open the BBB in rats (8). Through a series of studies, we have determined that the optimal parameters for SMES are 2/100 Hz, 3 mA, 6 s on and 6 s off (6–6 s), with a total stimulation duration of 40 min (8–10). Further research revealed that the effect of SMES on opening the BBB exhibits a time window, is dependent on the duration of stimulation, and is reversible (9, 11). Moreover, SMES-induced BBB opening does not cause adverse effects such as cerebral edema, glial cell activation, or neuronal apoptosis (9). The SMES applied at GV20 and GV26 acupoints has been shown to decrease the expression of tight junction proteins ZO-1 and occludin within the BBB, which can explain part of the potential mechanism of SMES opening the BBB (12). Additionally, SMES can induce NGF to cross the BBB, thereby improving motor and cognitive functions in rats during the recovery phase of middle cerebral artery occlusion/reperfusion (MCAO/R) (12). Another randomized controlled trial by our team, which is awaiting publication, investigating SMES combined with NGF for ischemic stroke, has shown significant therapeutic efficacy on motor and cognitive function and good safety (13).

These studies further consolidate our central hypothesis that the application of SMES to open the BBB will facilitate the delivery of exogenous NGF to achieve effective concentrations within the injured brain of post-stroke patients. We hypothesize that this approach can also benefit patients with PSD. Our team plans to conduct a pilot randomized controlled clinical trial on the treatment of dysphagia after ischemic stroke using SMES combined with NGF, to assess its effectiveness and safety.

To separately test the “BBB-opening carrier effect” of SMES, the “neuro-reparative effect” of NGF, their potential synergistic interaction, and to control for the non-specific effects of needling at the GV20 and GV26 acupoints themselves, we have adopted a 2 (SMES/Acupuncture) × 2 (NGF/Placebo) factorial, double-dummy design. This design aims to isolate and quantify the independent and combined contributions of each intervention component, providing a foundation for future mechanistic exploration and treatment optimization.

Functional near-infrared spectroscopy (fNIRS) can indirectly monitor cerebral cortical functional activity through changes in the concentrations of oxyhemoglobin (HbO2) and deoxyhemoglobin (HbR). Many fNIRS-based neuroimaging studies revealed that improved swallowing recovery in PSD is associated with upregulated activation patterns in the cortical swallowing network and strengthened functional integration among specific regions (14). We incorporated fNIRS into our study and integrated it with clinical efficacy assessments to investigate whether changes in swallowing function are associated with the therapeutic effects of SMES combined with NGF.

## Methods

### Study design

This study is a single-center, randomized, double-dummy, sham-controlled, four-arm parallel trial conducted at the Third Affiliated Hospital of Zhejiang Chinese Medical University. The schedule of enrolment, intervention, and assessment is shown in Figure 1. The flow chart is shown in Figure 2. The study protocol will be drafted in accordance with the guidelines of the Standard Protocol Items: Recommendations for Interventional Trials (SPIRIT) (15). The study conforms to the principles of the Declaration of Helsinki (16) and has been approved by the Medical Ethics Committee of the Third Affiliated Hospital of Zhejiang Chinese Medical University (ethical number: ZSLL-KY-2024-074-01). This trial has been registered at www.clinicaltrials.gov (NCT: NCT06737549) on December 12, 2024. Informed consent will be obtained from each participant before the performance of any study-specific procedure.

**Figure 1 fig1:**
[figure not shown]
Schedule of enrollment, intervention, and assessment.

**Figure 2 fig2:**
[figure not shown]
Flow chart of the study.

### Participants and recruitment

A total of 144 participants will be recruited through the notices posted in the hospital or on websites and social media (WeChat) from December 2024 to December 2027. The research assistants will be in charge of the recruitment, and neurological experts will be in charge of the diagnosis of the participants.

### Randomization and allocation concealment

One hundred forty-four eligible participants who have affirmed and signed informed consent will be randomly assigned in a ratio of 1:1:1:1 into the electroacupuncture (EA) + NGF group, the EA + placebo group, the acupuncture + NGF group or the acupuncture + placebo group, each with 36 participants, via a central randomization system, which is managed by a third-party mathematician outside the study and used to generate and conceal the allocation sequence. The randomization sequence will be generated in varying block sizes.

### Blinding

Participants, outcome assessors, and statisticians will remain blinded to treatment allocations. However, as the interventions (acupuncture or EA combined with either NGF or placebo) require direct physical contact with participants, the practitioners administering these interventions cannot be blinded. All participants will be treated separately to prevent communication. Except for acupuncturists, all relevant parties will be blinded to the intervention groups. Participants will be informed that they have an equal chance of allocation to each group before study participation.

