### EA + NGF group

A 20 μg dose of mNGF will be dissolved in 2 mL of sterile water for intramuscular injection into the gluteus maximus. Thirty minutes after injection, participants will receive EA treatment. The acupoints GV20 and GV26 will be acupunctured (Figure 3). Participants will lie in the supine position and relax. Prior to acupuncture, 75% alcohol pads will be used to sterilize the skin around the acupuncture points. For GV20, an acupuncture needle (0.25 mm × 40 mm) will be inserted transversely toward the central point of the posterior hairline to a depth of 15–20 mm. For GV26, an acupuncture needle (0.25 mm × 25 mm) will be inserted toward the nasal septum to a depth of 5–10 mm. Acupoints will be stimulated manually until participants feel soreness, distension or heaviness (the reaction of “De Qi”). Then, the needles will be stimulated using an acupuncture point nerve stimulator at a frequency of 2/100 Hz and an intensity tolerable to the participant (targeting 3.0 mA) for 40 min. A specially made relay cycles power to the electrodes in a 6-s on/6-s off pattern. The needles at both acupoints will be retained for 40 min. Participants will receive 18 treatment sessions, 3 times per week for 6 weeks.

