### Acupuncture + NGF group

Participants will receive an intramuscular injection of 20 μg mNGF into the gluteus maximus, as in the EA + NGF group. Thirty minutes after injection, participants will receive acupuncture treatment. The treatment protocol will be similar to that of the EA + NGF group, except that the needles will be connected to an acupuncture point nerve stimulator without actual current output. The device will display a frequency of 2/100 Hz and a current strength of 3.0 mA for 40 min, and a specially made relay will cycle in a 6-s on / 6-s off pattern. When switched on, the apparatus produces the same indicator lights and sounds as the active device but delivers no electrical current. The needles at both points will be retained for 40 min. Participants will receive 18 treatment sessions, 3 times per week for 6 weeks.

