Multimodal findings from clinical, electrophysiological, and imaging studies suggest that dysphagia recovery after stroke involves neuroplastic changes in the contralesional hemisphere across sensory, motor, and white matter domains (31–39). This body of evidence supports a compensatory model of contralesional neuroplasticity as the driving mechanism for recovery (1). fNIRS and electroencephalography (EEG) are two convenient brain function imaging techniques that have attracted significant attention in recent years and have yielded numerous significant findings on the mechanism of acupuncture’s effects on the brain (14, 40–42). Currently, the application of EEG in the study of PSD remains limited, but many fNIRS studies have proved that the effect of acupuncture can upregulate activation patterns in the cortical swallowing network and strengthen functional integration among specific regions (14). This study is not focused on the direct cerebral effects of acupuncture. Instead, fNIRS was chosen as the research method to examine the swallowing network recovery induced by NGF. In terms of study design, the four-arm study can highlight the interaction effect between SMES and NGF, and distinguish it from the independent effect of acupuncture at the GV20 and GV26 acupoints.

In China, a significant proportion of PSD patients have prior acupuncture experience, making patient blinding challenging (43). Thus, conventional acupuncture rather than sham acupuncture will serve as the control to optimize blinding feasibility.

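### Participant blinding to the EA factor is stated without qualification, but a current set to tolerance is compared with no current and nothing described masks its sensation, so that blind is not assured

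*Protocol article*

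**What the plan says.** All references are to the protocol article.

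- **Blinding** states "Participants, outcome assessors, and statisticians will remain blinded to treatment allocations" and then "Except for acupuncturists, all relevant parties will be blinded to the intervention groups". On what participants know, it states "Participants will be informed that they have an equal chance of allocation to each group before study participation".
- **EA + NGF group**: the needles are stimulated "at a frequency of 2/100 Hz and an intensity tolerable to the participant (targeting 3.0 mA) for 40 min", with a relay switching the current 6 s on and 6 s off. **EA + placebo group** uses the same EA procedure.
- **Acupuncture + NGF group**: the procedure matches that of the EA arms, with one stated difference: "except that the needles will be connected to an acupuncture point nerve stimulator without actual current output". The screen of the inactive stimulator nevertheless shows the nominal target of 3.0 mA, and its lights and sounds match the active device. **Acupuncture + placebo group** follows the same procedure.
- **Blinding assessment** plans Bang's Blinding Index at week 6.
- **Discussion** calls patient blinding challenging because many patients have had acupuncture before, and concludes that "conventional acupuncture rather than sham acupuncture will serve as the control to optimize blinding feasibility".
- The **limitations** in the Discussion name the unblinded acupuncturists as a source of performance bias. They do not mention participants. **Study design** calls the trial sham-controlled.

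**The concern.** The blinding statement covers participants in full, yet the one planned difference between the two levels of the EA factor is something a participant would be expected to feel. The reason given for the comparator concerns needling, which is the same in all four arms. It does not reach the current.

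The primary outcome, FOIS, grades what a patient takes by mouth and by which route. A participant who believes that the active or the inactive stimulation was given may differ in willingness to try textures, in effort during the five-day-a-week swallowing training, or in staying in the trial. Blinded assessors do not close that route, because it works through the participant's behaviour and not through the rating. This pathway is plausible, but the document does not measure it. At stake is whether a difference between EA and acupuncture arms can be read as an effect of the current.

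**Working it through.** The plan gives no figure for blinding success, so there is none to reproduce. The check sets the text side by side, works out which contrasts are exposed, and illustrates what the planned index could show.

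**1. What differs on the EA factor and what masks it**

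| Feature | EA arms | Acupuncture arms | Masked? |
|---|---|---|---|
| Needling at GV20 and GV26 | yes | yes | yes, identical |
| Lights and sounds | yes | yes | yes, stated to match |
| Injection 30 min before | NGF or saline | NGF or saline | not part of the EA factor |
| Current through the needles | to tolerance, target 3.0 mA | none | no masking of sensation described |

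That the current is felt is an inference. It follows from the protocol's own rule, since intensity cannot be set to what a participant tolerates unless the participant perceives it.

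**2. How many participants and how often**

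- 36 per arm x 2 arms = 72 with current; 36 x 2 = 72 without; 72 + 72 = 144.
- If the 40 min include the off periods (assumption), one session has 40 x 60 / (6 + 6) = 200 on-periods. Over 18 sessions that is 200 x 18 = 3,600.
- These numbers count exposure to the cue, not participants unblinded.

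**3. Which contrasts are exposed**

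Let m be the true mean in each arm. Let bE be an expectation effect common to both EA arms and bA one common to both acupuncture arms.

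- EA main effect: ½[(m_EA,NGF + m_EA,Pla) − (m_Acu,NGF + m_Acu,Pla)] + (bE − bA). Biased by bE − bA.
- EA + NGF versus acupuncture + NGF: m_EA,NGF − m_Acu,NGF + (bE − bA). Biased by the same amount, as is every other pairwise comparison across EA levels.
- NGF versus placebo within EA: (m_EA,NGF + bE) − (m_EA,Pla + bE) = m_EA,NGF − m_EA,Pla. Not biased. The same holds within acupuncture.
- EA x NGF interaction: the difference of the two within-level contrasts, from which bE and bA both cancel. Not biased if the effect is additive.
- Non-additive case: FOIS stops at 7. If the expectation gain is bE in EA + placebo but only a fraction f of it in EA + NGF because more patients sit near the top, the interaction shifts by (f − 1) x bE. For a positive bE and f below 1 this is against synergy. An effect that is additive on the score scale is also not additive on the logit scale proposed for the GEE.

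**4. What the planned index could show (assumed guess rates)**

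Bang index = proportion correct − proportion incorrect = 2p − 1, assuming no don't-know answers. Standard error = 2 x √(p(1 − p)/n). With n = 72 per EA level:

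| Correct guesses p (assumed) | Index | 95% CI |
|---|---|---|
| 50% | 0.00 | −0.23 to 0.23 |
| 60% | 0.20 | −0.03 to 0.43 |
| 70% | 0.40 | 0.19 to 0.61 |
| 80% | 0.60 | 0.42 to 0.78 |
| 90% | 0.80 | 0.66 to 0.94 |

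By arm, with n = 36 and p = 50%, the half-width is 1.96 x 2 x √(0.25/36) = 0.33. The index can therefore detect marked unblinding, but it is imprecise for moderate unblinding and prevents neither.

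**The case against.** The strongest reply is that the trial does more than many to mask this factor. Every arm receives real needling to De Qi, the inactive device has the same lights and sounds, participants are treated separately, and a Bang index is planned. The Discussion admits that blinding patients is hard. The limitations also say that superiority of SMES + NGF would need confirmation under strict sham controls. An article need not print operator scripts or consent wording, and those may exist elsewhere. This is a limitation common to no-current controls, in a self-described pilot.

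Much of that stands, and it limits the point in four ways.

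- A reader might infer that the blind must fail. The document does not show this: it reports neither how perceptible the current is nor how often participants guess correctly.
- A reader might infer that the interaction, which is the trial's central question, is biased towards SMES. Step 3 of the working shows that a common expectation effect cancels on an additive scale. Under a ceiling the shift could go the other way.
- A reader might infer that a display reading below 3.0 mA gives the active arms away. Participants lie supine and the screen position is not stated. The control procedure is called similar apart from the current, which is compatible with the same adjustment routine.
- Assessor and statistician blinding, claimed in the same sentence, is not contradicted by any of this.

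What the reply does not answer is that the blinding statement is categorical for participants, while the intervention sections describe an unmasked sensory difference. The planned index measures the result at week 6, after the sessions. The limitations leave participant unblinding out.

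**Conclusion.** Participant blinding to the EA factor is claimed without qualification but is not assured by the procedures described. The EA main effect and all pairwise comparisons across EA levels, including EA + NGF versus acupuncture + NGF, are open to expectation bias. NGF versus placebo within an EA level is not open to it by this mechanism. The interaction is affected only through non-additivity, such as a ceiling or the choice of scale.

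The conclusion rests on two assumptions: that a current set to tolerance is usually felt, and that belief can influence oral intake, effort or retention. All 144 participants are on one or the other side of the contrast, but the proportion who would guess correctly, and hence the bias on FOIS, cannot be derived from the document. The point is worth correcting because the changes are cheap. It is no ground for dismissing the factorial design.

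**What to change.** - **EA + NGF group and Acupuncture + NGF group** (carried to the other two arms by reference): specify one scripted intensity-adjustment routine for all four arms, with the inactive output kept at zero. State that the display is handled identically in every arm.
- **Participant information**: tell everyone that the current may or may not be felt and that this does not indicate the group.
- **Blinding**: describe participant blinding to the EA factor as attempted and to be verified by the planned week 6 Bang index.
- **Blinding assessment and Statistical analysis**: report the index by arm for the guess about current. State that EA main-effect results and pairwise results across EA levels will be interpreted in the light of it.
- **Limitations**: add possible participant unblinding on the EA factor next to the unblinded acupuncturists.

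If the full protocol already contains such a routine or wording, only the last three changes are needed. The cost is a small amount of operator training, an edit to the protocol and participant information, and a slightly less favourable blinding claim.

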### Participants

#### Inclusion criteria

Participants will be eligible if they:

(1) Have a first-ever ischemic stroke confirmed by Computed Tomography (CT) and/or Magnetic Resonance Imaging (MRI); (2) have an onset time ranging from 31 days to 90 days; (3) are aged 18 to 80 years, male or female; (4) have dysphagia confirmed by video fluoroscopic swallowing study (VFSS); (5) are able to accept and comply with acupuncture, EA treatment, gluteal intramuscular injection; (6) have already signed consent and exhibit willingness to participate in the trial.

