#### Exclusion criteria

Participants will be excluded if they:

(1) Had dysphagia before this ischemic stroke onset or dysphagia not caused by ischemic stroke; (2) have severe cognitive impairment; (3) have a history of multiple strokes, craniocerebral surgery, or cerebral space-occupying lesions; (4) have severe cardiac, hepatic, or renal dysfunction, or other abnormal test results that make the patient unsuitable for participation in this study; (5) have severe neurological deficits prior to ischemic stroke, such as visual and auditory impairments, aphasia, agnosia, severe hemiplegia, and other conditions; (6) are women who are lactating, pregnant or planning pregnancy; (7) have a history of needle fainting or with skin infections at the acupuncture sites; (8) are carriers of a cardiac pacemaker; (9) have a known allergy to NGF; (10) are unable to undergo VFSS; (11) have taken medications that may alter cortical excitability within the past 2 months; (12) are currently participating in other clinical trials or have participated in clinical trials that ended within the last 3 months.

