### Outcomes

#### Primary outcome

The primary outcome is the Functional Oral Intake Scale (FOIS) (20), which reflects the overall intake capability based on swallowing function. The FOIS is a 7-point ordinal scale with a score range of 1–7. Oral intake ability is measured in terms of intake method and food type. Higher scores indicate better oral intake ability. Assessment time frames: at baseline; at week 2, 4, 6, and 12. Week 6 post-intervention is the primary endpoint.

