### Statistical analysis

The overall dropout rate and the dropout rate due to adverse events will be calculated for each group. It will be statistically determined whether each group received the treatment as specified in the study protocol in terms of duration and number of sessions, and the number and percentage of subjects with compliance < 80% will be calculated. Efficacy analysis will be performed in the full analysis set. Participants who have been randomized and have received at least one treatment session will be included in the full analysis set (FAS). All hypothesis tests will be two-sided, and *p*-value < 0.05 will be considered to indicate statistical significance of the tested difference. For ordinal outcomes (FOIS, DOSS, PAS, and mRS), non-parametric tests (Kruskal–Wallis *H* test for group comparisons, with post-hoc Mann–Whitney *U* tests and alpha adjustment) will be used for cross-sectional analyses. For longitudinal ordinal outcomes, generalized estimating equations (GEE) with an appropriate link function (e.g., logit) and working correlation matrix will be the primary method for analyzing these outcomes across multiple time points (FOIS, mRS). The normality of continuous data (MBI, fNIRS metrics) will be assessed using the Shapiro–Wilk test. Provided that parametric assumptions are met, (repeated-measures) ANOVA will be applied. Should the assumptions be violated, non-parametric alternatives (e.g., Kruskal–Wallis test, Friedman test) will be used. The study results will include three-factor (EA factor/NGF factor/time factor) repeated-measure data, with measurement data analyzed using three-factor repeated-measures analysis of variance and ordinal data analyzed using the generalized estimating equation (GEE) to test for differences. The Bonferroni method will be used to adjust for the significance of multiple comparisons.

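### Infarct site is unrestricted at entry and absent from the named analyses; prespecifying it as a covariate is an inexpensive, optional gain in precision whose size is uncertain.

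*Protocol article*

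**What the plan says.** **Eligibility.** Inclusion criterion 1 is "Have a first-ever ischemic stroke confirmed by Computed Tomography (CT) and/or Magnetic Resonance Imaging (MRI". No exclusion criterion names infarct site; the nearest one removes patients who "have a history of multiple strokes, craniocerebral surgery, or cerebral space-occupying lesions".

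**Randomisation.** Under Randomization and allocation concealment, participants "will be randomly assigned in a ratio of 1:1:1:1", 36 to an arm. The only detail given of the sequence is "The randomization sequence will be generated in varying block sizes". No stratification factor is named.

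**Analysis.** For FOIS, "Week 6 post-intervention is the primary endpoint". Statistical analysis assigns cross-sectional comparisons of FOIS, DOSS, PAS and mRS to "non-parametric tests (Kruskal–Wallis *H* test for group comparisons, with post-hoc Mann–Whitney *U* tests and alpha adjustment"). GEE is the primary method for FOIS and mRS across time points. The factors are given in this sentence: "The study results will include three-factor (EA factor/NGF factor/time factor) repeated-measure data". No baseline covariate is mentioned.

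**Rationale.** The Introduction presents a 2 × 2 factorial design meant to separate the SMES effect, the NGF effect and their interaction. The Discussion says of the literature on swallowing recovery: "This body of evidence supports a compensatory model of contralesional neuroplasticity as the driving mechanism for recovery". The fNIRS channels are grouped into eight regions, four on each side.

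**The concern.** Brainstem or cerebellar infarcts and hemispheric infarcts can all enter the trial. If swallowing recovers differently after the two kinds, week-6 FOIS will vary with infarct site. That variation then sits in the error term of every arm comparison. Site is fixed before treatment and visible on the qualifying scan, so leaving it out gives up precision that would be almost free.

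This matters most where precision is scarcest, on the interaction between SMES and NGF, which the Introduction makes a central aim. There is a further reason to look at fNIRS. The contralesional model in the Discussion is most naturally read for a lesion in one hemisphere, and it may not carry over directly to an infratentorial infarct, where neither cortex is lesioned.

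**Working it through.** **The plan's own figure.** Sample size starts from 30 per arm and allows for 20% dropout: 30 × 1.20 = 36, and 4 × 36 = 144. This reproduces the stated enrolment. No effect size, SD or power is given, so the plan has no precision figure to compare with.

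**Assumptions (not in the documents).** Let *p* be the infratentorial share, 0.20–0.40. Let *d* be the gap in mean week-6 FOIS between sites, in within-site SDs: 0.3, 0.5 or 1.0. FOIS is treated as roughly continuous.

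**Variance share.** The variance of an unadjusted contrast is SE² × [1 + p(1−p)d²]. The second term is the part that comes from chance differences in site share between arms. Imbalance and avoidable variance are therefore largely one cost and should not be counted twice. The removable share is R² = p(1−p)d² / [1 + p(1−p)d²].

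| d | p(1−p)d² at p = 0.20; 0.40 | R² | R² × 144 |
|---|---|---|---|
| 0.3 | 0.0144; 0.0216 | 1.4–2.1% | 2–3 participants |
| 0.5 | 0.040; 0.060 | 3.8–5.7% | 6–8 |
| 1.0 | 0.160; 0.240 | 13.8–19.4% | 20–28 |

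**Where it is felt.** Standard errors with 36 per arm, in within-site SDs:
- Main effect, 72 vs 72: √(2/72) = 0.167
- Two single arms: √(2/36) = 0.236
- Interaction (difference of differences): √(4/36) = 0.333

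The proportional gain is the same for all three, but the interaction starts with twice the standard error of a main effect. Multiplying 0.333 by √(1 + p(1−p)d²), the unadjusted interaction SE is about 0.336–0.337 at d = 0.3, 0.340–0.343 at d = 0.5 and 0.359–0.371 at d = 1.0. Adjustment would bring each back to about 0.333.

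**Chance imbalance.** Treating site as binomial within arms, the probability of an imbalance of at least 15 percentage points in site share is:
- Main effect: 3–7%
- One given pair of arms: 10–19%
- Interaction contrast: 25–35%

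A 15-point imbalance moves the contrast by 0.15 × d, that is 0.045, 0.075 or 0.15 SD. Each is below the corresponding standard error.

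**Cross-check in FOIS points.** Assume a within-site SD of 1.5, a site gap of 1 point and a treatment effect of 1 point, with 30 per arm and two-sided 0.05. For shares of 20–50%, R² is 7–10%, and pairwise power rises from 69–70% to 73%.

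**Baseline FOIS.** These figures treat the whole site effect as error. FOIS is measured at baseline and at weeks 2, 4, 6 and 12. If the GEE tests group by time with baseline included, a stable difference in level between sites is largely removed, and only the effect of site on change remains. The gain is then smaller than shown.

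**The case against.** The strongest reply is that this rests partly on silence. The full protocol and SAP are not shown, and they are where covariates are usually listed. The sentence on EA, NGF and time describes the data structure and does not exclude baseline covariates in the GEE. That stands for the GEE. It does not help the rank tests, which the article commits to and which take no covariate.

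Second, the prognostic effect of site is not in the documents. The Discussion never mentions brainstem, cerebellar or infratentorial infarcts, and its contralesional model is background to the choice of fNIRS. Different recovery routes need not mean different FOIS levels at week 6. This stands, and it is why the size is given as a range that starts near nothing.

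Third, site is one candidate covariate among several in a self-described pilot, and the Discussion already concedes that the sample is small. That also stands, and it argues for treating the point as optional. The trial nevertheless tests effectiveness at 0.05, so precision is of some value.

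A reader might go further and infer that unstratified allocation biases the comparison or inflates type I error. It does neither: chance imbalance averages out, and the ordinary standard error already includes it. A reader might also infer that patients with infratentorial infarcts have no contralesional hemisphere. The documents do not say so, and a unilateral brainstem or cerebellar infarct still has a side.

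**Conclusion.** The point holds as a modest, optional improvement to the analysis. Entry is open to any infarct site, and no named analysis uses site, although it is known before randomisation. The validity of the trial is not in question.

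The cost is possible lost precision on week-6 FOIS, of most consequence for the SMES × NGF interaction. For an assumed infratentorial share of 20–40%, it is about 1–2% of variance at a site effect of 0.3 SD, 4–6% at 0.5 SD and 14–19% at 1.0 SD, and less where baseline FOIS is already in the model. Both the share and the effect are assumptions. At the low end the gain is worth only 2–3 of 144 participants.

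The documents do not support a demand to stratify the randomisation. The recruitment window opened in December 2024, and covariate adjustment recovers most of what stratification would offer.

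**What to change.** - Record infarct site (infratentorial or supratentorial) from the qualifying CT/MRI.
- In the GEE for FOIS and mRS, prespecify site as a fixed covariate alongside baseline score.
- For week-6 DOSS and PAS, which have no model to receive a covariate, replace the unadjusted rank tests. Either use a proportional-odds model with EA, NGF, EA × NGF, baseline score and site, or use site-stratified (van Elteren) tests. The model also gives the interaction; the stratified tests give only arm comparisons.
- Include site as a covariate in the fNIRS group comparisons.
- Leave the randomisation list as it is.

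The cost is one extra data field, one degree of freedom per model, and replacement of the DOSS and PAS rank tests, which is more than a wording change. With a logit link, the adjusted odds ratio is conditional on site and should be reported as such.
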